### **6-Week Follow-up evaluation:**

All the measures evaluated at the baseline visits will be repeated at six weeks after completion of the second intervention.

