### **Statistical Analysis:**

For the observational phase, exploratory analyses will be undertaken to determine how well scores on the electrographic outcomes (evoked potentials, H-reflex testing, computerized posturography, surface electromyography) correlate with clinical outcomes such as gait disability, gait speed, and AIS motor and sensory scores. Using post hoc regression analysis, we hope to generate a preliminary model to predict anatomical and functional integrity of specific neural tracts based on performance on this battery of tests. This analysis and any resulting predictive model would need further validation with a prospectively studied population. The interventional phase of the study would not depend on the success of obtaining such a predictive model.

For the interventional phase of the study, participants will be randomly assigned to receive either locomotor training followed by multimodal training, or multimodal training followed by locomotor training. The primary outcomes will be change in tibialis anterior motor-evoked potential amplitude and change in lower extremity motor score (LEMS) compared to baseline. All other outcomes are secondary and exploratory.

The most rigorous method of analyzing data from crossover studies involves the use of independent-sample rather than paired-sample tests (Wellek & Blettner 2012). Therefore, outcome measures will be calculated within each subject as the percent change between baseline and completion of each intervention. The percent change across all subjects for each training modality will be compared using independent-sample t-tests or Mann-Whitney U tests depending on the normality of the data distribution. To test for the possibility that the washout period does not fully eliminate carryover effects, the percent change across all subjects for each training period (pre-washout, post-washout) will also be compared using independent sample tests. Statistical significance for all outcomes will be corrected for multiple comparisons using Bonferroni's method.

**Power Calculation:** Given that our training protocol is novel, we need to make predictions by extrapolating from other types of protocols. This is further hampered by the fact that most SCI

rehabilitation studies involve rather small numbers of participants in often inadequately controlled studies.

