The most applicable study upon which to base our power analysis measured MEP amplitudes before and after 60-100 sessions of treadmill training in eight subjects with incomplete thoracic SCI (Thomas & Gorassini 2005). They found a  $46 \pm 12\%$  increase in maximal MEP amplitude post-training. Additionally, studies in uninjured volunteers demonstrated a 40-70% increase in MEP amplitudes with skilled training exercises but not passive movement or strength training (Jensen et al. 2005; Perez et al. 2004).

Due to these and other factors, we project an improvement of 50% with MULTIMODAL training versus 25% with TREADMILL training. The use of a crossover design will reduce inter-subject variability between the two training modalities compared to a parallel-group design. We conservatively project an estimated variance of 25% for each group – this magnitude of variance is larger than the average variance seen in the MEP studies cited above. Based on these numbers, the calculated power to detect a difference between the two training groups on a two-tailed independent-sample *t*-test or Mann-Whitney test is greater than 80% with 18 subjects, at an  $\alpha = 0.05$ . We will enroll 24 subjects to account for up to a 25% dropout rate.

|                | Year 1 | Year 2 | Year 3 | Total N |
|----------------|--------|--------|--------|---------|
| Phase 1 | 15     | 18     | 18     | 51      |
| Phase 2 | 6      | 10     | 8      | 24      |

**Table 3** Clinical Study Timeline – Participants enrolled per year.

**3a. Basic Information** (Even if described under “Procedures”, list the information requested below where pertinent.)

The study will occur in two phases: An observational phase, in which participants will undergo a series of clinical and neurophysiological tests; and an interventional phase, in which participants with incomplete SCI will undergo standard LOCOMOTOR training and experimental MULTIMODAL training in random order. Training will continue for 48 sessions per intervention, separated by a 6-week washout period. The clinical and neurophysiological tests will be repeated at the end of each intervention.

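### The planned carryover check compares period 1 with period 2, so it mixes the period effect with average carryover and cannot see the carryover difference that biases the modality comparison

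*Protocol*

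**What the plan says.** The interventional phase is a two-sequence, two-period crossover: "participants will be randomly assigned to receive either locomotor training followed by multimodal training, or multimodal training followed by locomotor training" (Protocol, section 3, *Statistical Analysis*). A six-week washout separates the periods (*Training Schedule*).

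The modality comparison pools both sequences: "The percent change across all subjects for each training modality will be compared using independent-sample t-tests or Mann-Whitney U tests". The carryover check follows in the same paragraph. Its purpose is "To test for the possibility that the washout period does not fully eliminate carryover effects", and its method is that "the percent change across all subjects for each training period (pre-washout, post-washout) will also be compared using independent sample tests". No comparison between the two sequence groups is described, no separate test is named for a period effect, and no action is tied to the result of the check.

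Under *Post-training evaluation*, all baseline measures are repeated at the start and end of each training period, so a period-2 starting value exists. Under *6-Week Follow-up evaluation*, "All the measures evaluated at the baseline visits will be repeated at six weeks after completion of the second intervention".

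**The concern.** A pre-washout versus post-washout comparison pooled over sequences is the usual contrast for a period effect. Learning, fatigue or a ceiling on improvement would move it with no carryover at all. Carryover harms the modality comparison only when the two trainings carry over by different amounts, and that difference cancels out of the pooled period contrast.

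Carryover is a serious possibility here. The hypothesis is that training strengthens and reroutes neural connections, which is meant to persist. The protocol also uses the same six-week interval both as the washout and as the delay at which it looks for effects after the second training. This check is the only safeguard against carryover that the protocol names. A non-significant result could be reported as evidence of an adequate washout, and a plain period effect as evidence of an inadequate one. Neither conclusion would follow.

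**Working it through.** **Inputs from the protocol** (*Statistical Analysis*, *Power Calculation*). The projection is "we project an improvement of 50% with MULTIMODAL training versus 25% with TREADMILL training". The stated variance of 25% is read as an SD of 25 points. The test is two-sided at 0.05 with 18 participants, and 24 are enrolled.

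**Assumptions.** Sequences are equal (9 + 9). Carryover adds to the period-2 change score. The within-participant correlation is 0 to 0.5. Sizes of period effect and carryover are illustrative, because the protocol gives none. Rates are before the Bonferroni correction.

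**The plan's own figure.** Standardised difference = 25/25 = 1; noncentrality = 1 × √(18/2) = 3. Power is 0.85 by the normal approximation and 0.83 by the noncentral t with 34 degrees of freedom. This agrees with the stated figure of over 80%, counting 18 values per modality. Dropout: 18/(1 − 0.25) = 24. The power statement reproduces.

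**Expected values.** Let tM and tL be the training effects, π the period effect, and λM and λL the carryovers of multimodal and locomotor training into period 2.

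| Sequence | Period 1 | Period 2 |
|---|---|---|
| Multimodal first | tM | tL + π + λM |
| Locomotor first | tL | tM + π + λL |

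- Planned check, period 2 − period 1: **π + (λM + λL)/2**
- Modality contrast, multimodal − locomotor: **tM − tL + (λL − λM)/2**
- Participants' two-period sums, multimodal-first − locomotor-first: **λM − λL**, free of π

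The bias is (λL − λM)/2, and nothing in the check estimates it. Example with λM = 25, λL = 0, π = 0: the check expects 0 + (25 + 0)/2 = 12.5, and the modality contrast becomes 25 + (0 − 25)/2 = 12.5. If π = −12.5, the check expects −12.5 + 12.5 = 0 and the bias is unchanged.

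**Simulation** (t-tests, 9 per sequence, SD 25, 40,000 trials per scenario; ranges cover correlations 0 to 0.5):

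| Scenario | Expected modality estimate | Planned check fires | Sequence-sum test fires |
|---|---|---|---|
| Period effect −25, no carryover | 25 (unbiased) | 76-84% | 5% |
| Both trainings carry over +25 | 25 (unbiased) | 76-84% | 5% |
| Multimodal only, +25 | 12.5 | 20-27% | 21-29% |
| Multimodal only, +25, period effect −12.5 | 12.5 | 0.4-4% | 21-29% |
| Multimodal +25, locomotor +12.5 | 18.75 | 53-54% | 9-11% |
| Multimodal −20, locomotor +20, no true difference | 20 (spurious) | under 3% | 46-62% |

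In the third row the planned modality test itself is significant in only 20-27% of trials. In the last row the spurious effect is significant in about 58-61%.

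**Independence.** Both samples are the same participants. With positive correlation the independent-samples test is conservative: with no period effect or carryover and the projected 25-point modality difference, it rejects in about 1% of trials or fewer at correlations of 0.3 to 0.5, against a nominal 5%.

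**Unequal sequences.** If dropout left 12 multimodal-first and 6 locomotor-first, the period means would be (12 × 50 + 6 × 25)/18 = 41.7 and (12 × 25 + 6 × 50)/18 = 33.3. That is a period difference of −8.3 points produced by the modality effect alone.

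**The case against.** The strongest reply is that the check is not blind to carryover. Its stated purpose is to detect incomplete washout, without limiting this to unequal carryover, and the average carryover is one of its two terms. If both trainings carry over by 25 points it fires in 76-84% of trials. With same-sign carryovers of 25 and 12.5, which suits the rewiring hypothesis better than opposite signs, it fires far more often than the sequence-sum test (53-54% against 9-11%). This stands. A reader might infer that the test has nothing to do with carryover, and the algebra does not support that. The defect is that average carryover cannot be told apart from a period effect, and that the harmful difference is absent.

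The exactly opposite carryovers (−20 and +20) are contrived, and nothing in the protocol suggests them. They are a worst case only; the one-sided scenario makes the point without them.

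A reader might also infer that a misleading result would change the analysis. The protocol attaches no decision to the check, and the modality test runs regardless. The harm is in interpretation.

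The additive model is also a choice. The outcome is defined so that "outcome measures will be calculated within each subject as the percent change between baseline and completion of each intervention", and it is not clear whether baseline means study entry or the start of each period. With a period baseline, a persisting gain shifts the starting value and the denominator and would not simply add to the change. The sizes above would then differ; the inability of a pooled period contrast to show a difference between sequences would not. The figures concern motor evoked potential amplitude only, since the protocol projects no effect for the motor score.

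**Conclusion.** The concern holds in this limited form. The stated check estimates the period effect plus average carryover, cannot separate the two, and carries no information on the carryover difference that biases the modality comparison. In the scenarios examined, it raises a false carryover signal in about 76-84% of trials under a pure 25-point period effect. It also misses, in most trials, a one-sided carryover that halves the projected effect: it fires in 20-27%, or 0.4-4% when a period decline masks it.

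These sizes rest on the plan's 50/25 and SD 25, equal sequences of 9, additive carryover, and assumed period and carryover effects. The algebra needs only additivity and equal sequences. Because the protocol writes this test out, it is not a detail left for later. It should be corrected, but it is not a must-fix: the check is a secondary diagnostic with no stated consequence, and correcting it does not remove any bias from the primary estimate.

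**What to change.** Amend the sentence in *Statistical Analysis* as follows.

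- Call the pre-washout versus post-washout comparison a period-effect check. Calculate it from within-participant differences, by sequence, and then average the two sequences, so that pairing is respected and unequal sequence sizes do not let the modality effect leak in.
- For carryover, compare each participant's sum of the two period changes between the sequence groups.
- Also compare the period-2 starting values with the period-1 baseline, by sequence.
- Report all of these as estimates with confidence intervals.

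The cost is a few lines of text. The start-of-period assessments are already scheduled, so no visits, participants or measurements are added.

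The drawback is low power: the sequence-sum comparison detects a one-sided 25-point carryover in only about 21-29% of trials. The text should therefore say that a non-significant result does not show that the washout worked.

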### **Secondary outcomes:**

1. Change from baseline in AIS sensory scores.
2. Change from baseline in Berg Balance Scale score.
3. Change in leg spasticity on modified Ashworth Scale, Spinal Cord Assessment Tool for Spasticity, and Spinal Cord Injury Spasticity Evaluation Tool.
4. Change in gait speed on 10-meter Walk Test.
5. Change from baseline in Walking Index for Spinal Cord Injury II (WISCI II) scale.

6. Change from baseline in total number of steps taken by both feet during seated 10-second step test.
7. Change from baseline in total number of successful grasp-and-release trials taken by each hand (for cervical-level participants only).
8. Change from baseline in pinch dynamometry strength (in cervical-level participants only).
9. Change in quality of life as determined by WHOQOL-BREF and SCIQoL questionnaires.
10. Change in subjective pain as determined by McGill Pain Questionnaire (short form).
11. Change in percentage of upper and lower extremity lean tissue mass.
12. Change from baseline in endpoint excursion and directional control parameters achieved during seated Limits of Stability testing.
13. Change from baseline in soleus H-reflex facilitation and inhibition using appropriately timed physical stimuli, subthreshold transcranial magnetic stimulation, peroneal and tibial nerve stimulation.
14. Change from baseline in the Voluntary Response Index (VRI) for key leg muscles as detected by surface electromyography (Lee et al. 2004).

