- McGill Pain Questionnaire (short form) – Chronic neuropathic pain commonly plagues subjects with SCI. This short (less than 5 minutes), validated survey will provide a baseline to track whether any neural plastic changes result in adverse effects on neuropathic pain.
- Spinal Cord Injury Spasticity Evaluation Tool (SCI-SET) - This survey evaluates how spasticity impacts a person's activities of daily living over the course of the previous 7 days. The survey uses a bidirectional Likert scale to detect both negative and positive impacts of spasticity (Adams et al. 2007).
- SCIQoL - Participants will complete a questionnaire regarding physical/medical health, emotional health, physical function, and social participation. A research assistant will conduct the interview. The questionnaire is located on an online platform called Assessment Center. The Assessment Center database is housed at Northwestern University and analyzed by a team at the University of Michigan. No HIPAA identifiers will be collected through the online platform.
- WHOQOL-BREF Questionnaire – This tool assesses general quality of life, and has been internationally validated for use in the SCI population. It is briefer than the computer-adapted SCI-QOL survey and will be used specifically to correlate with findings on the SCI-SET and SCATS (World Health Organization 1998).

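### Pain is measured to look for harm from training, but the stated Bonferroni-corrected comparison between trainings does not test whether pain rises

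*Protocol*

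**What the plan says.** Under Clinical Tests, the protocol explains that the short-form McGill Pain Questionnaire "will provide a baseline to track whether any neural plastic changes result in adverse effects on neuropathic pain". That is a question about harm.

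Under Secondary outcomes, change in pain is item 10 of 14. The Statistical Analysis section adds that "All other outcomes are secondary and exploratory".

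The same section sets the analysis for outcomes in general. Each is expressed within participant as a percent change from baseline to the end of each intervention. Then "The percent change across all subjects for each training modality will be compared using independent-sample t-tests or Mann-Whitney U tests". For carryover, "the percent change across all subjects for each training period (pre-washout, post-washout) will also be compared using independent sample tests". Finally, "Statistical significance for all outcomes will be corrected for multiple comparisons using Bonferroni's method". Pain is not exempted, and the number of comparisons is not given.

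Separately, under Protection against Risk, adverse events are recorded and reported to the IRB. No analysis of questionnaire scores is attached to that route.

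**The concern.** Whether training-induced plasticity worsens pain is a before-after question. The stated test asks a different one: whether the two trainings differ. The protocol's power calculation projects MEP gains under both trainings (50% and 25%), so on its own premises both may induce plastic change. If both raised pain, the contrast would remove the effect that the questionnaire was included to detect.

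Bonferroni adds a second problem. It limits false positive claims, which is sensible for claims of benefit. Applied to a harm outcome, it lowers the chance of seeing the harm.

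A smaller problem is the metric. Percent change is undefined for a participant whose baseline pain score is zero, so new-onset pain in that participant could not enter the analysis. The protocol calls neuropathic pain common in this population, not universal, so such participants are possible.

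At stake is whether the trial can say anything useful on a safety question that it raises itself.

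**Working it through.** **Inputs from the protocol.** Two-sided independent-samples test; 18 completers out of 24 enrolled (25% dropout); two primary outcomes and 14 numbered secondary items.

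**Assumptions.** Bonferroni divisor k = 2 + 14 = 16, so alpha = 0.05/16 = 0.003125 (range k = 14 to 30 shown below). Pain change is normal with SD 1 in each training, and effects are in SD units. The protocol gives no pain effect size.

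**Formula.** With n values per training and a true difference d, power = P(|T| > t(1 − alpha/2; 2n − 2)), where T is noncentral t with noncentrality d·√(n/2).

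**Step 1: the protocol's own figure.** For MEP, d = (50 − 25)/25 = 1.0, reading the stated variance of 25% as an SD. With n = 18 values per training, noncentrality = 1.0 × √9 = 3.0, the critical value is 2.032, and power = 83%. For Mann-Whitney, with efficiency 0.955, it is 81%. The stated figure of more than 80% reproduces at alpha 0.05, so the same method is applied to pain.

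**Step 2: pain rises equally under both trainings.** Then d = 0 whatever the size of the rise, and the rejection rate equals alpha: 0.3% with Bonferroni, 5% without. If a participant's two changes are positively correlated, the independent-samples test rejects even less often. In simulation with correlation 0.5, the rates are about 0.02% or less with Bonferroni and under 1% without.

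**Step 3: pain rises under one training only.** For n = 18 and d = 0.5, noncentrality = 0.5 × 3 = 1.5, and the critical value moves from 2.032 (alpha 0.05) to 3.181 (alpha 0.003125).

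| Rise | n = 18, alpha 0.05 | n = 18, k = 16 | n = 24, alpha 0.05 | n = 24, k = 16 |
|---|---|---|---|---|
| 0.5 SD | 31% | 6.1% | 40% | 9.6% |
| 0.8 SD | 65% | 24% | 77% | 38% |
| 1.0 SD | 83% | 44% | 92% | 63.5% |

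For k from 14 to 30 with n = 18, corrected power runs from 6.6% down to 4.0% at 0.5 SD, and from 46% down to 36% at 1.0 SD.

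**Step 4: the carryover comparison.** It contrasts the first period with the second. A rise present in both periods cancels there too, so it does not fill the gap.

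**Step 5: a direct look at change within a training.** The 95% CI half-width is t(0.975; n − 1)/√n: 2.110/√18 = 0.50 SD, or 2.069/√24 = 0.42 SD. Unadjusted one-sample power is 52% (n = 18) or 65% (n = 24) for a 0.5 SD rise, and 98% or over 99% for a 1.0 SD rise. This does not depend on what the other training does.

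**The case against.** Several objections carry weight.

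- **Reading of a null result.** A reader might infer that a true pain rise would be reported as no adverse effect. The protocol never says so. It calls the outcome exploratory, and its wording on the questionnaire is that of monitoring, not of a promised test. The inference is therefore not supported. What remains is that no other basis for a conclusion on pain is stated.
- **A real rise would almost always be missed.** This holds for a shared rise, and for a one-training rise up to about 0.5 SD. It does not hold for large differential rises: at 1.0 SD the corrected test detects 44% with 18 completers and 63.5% with 24.
- **Bonferroni as the main fault.** For a shared rise it is not: removing it lifts detection only to 5% or less, because the contrast is at fault. For a 0.5 SD one-training rise, 69% (n = 18) or 60% (n = 24) is missed even without it, because the sample is small.
- **Within-participant change is already calculated.** This is true, and a shared rise would be visible in those data. But the stated inference is drawn only from comparisons between trainings and between periods.
- **The randomised contrast is a legitimate safety question.** Whether the new training worsens pain more than standard training is worth asking, and an uncontrolled before-after change cannot separate training from fluctuation or regression to the mean. This stands, and is why the contrast should be kept.
- **Detail for the analysis plan.** Table layouts and intervals may be left there. The point here is different: the protocol itself fixes a rule for all outcomes that does not fit the purpose it gives this one.

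**Conclusion.** The concern holds in limited form. The analysis stated for pain does not answer the before-after harm question that the protocol attaches to the questionnaire. A rise common to both trainings is essentially invisible to it (flagged at most about 0.3% of the time with k = 16, at most about 5% uncorrected). For a rise confined to one training, Bonferroni costs 25 percentage points of power at 0.5 SD (31% to 6%) and 39 at 1.0 SD (83% to 44%) with 18 completers. With 24 completers, the falls are from 40% to 10% and from 92% to 63.5%.

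These sizes rest on an assumed divisor, assumed effects and normal data; the cancellation of a shared rise rests on none of them. The undefined percent change at a zero baseline also follows directly from the metric, although how many participants it would affect is unknown. The finding concerns one secondary outcome and does not touch the primary analysis. The change is worth making because the outcome serves safety and the remedy costs little.

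**What to change.** In the Statistical Analysis section:

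- Exempt the McGill score from the Bonferroni correction and treat it as a safety outcome.
- For each training, report the mean within-participant change in scale points from the start to the end of that training period, with an unadjusted 95% CI, and the number of participants whose score worsened. Scale points also remove the zero-baseline problem.
- Keep the randomised between-training difference, also with an unadjusted 95% CI.
- State that a claim of no worsening will not rest on a non-significant test, and read the upper confidence limits instead.

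The cost is a few sentences and one table, with no new data, visits or participants. There are two downsides. Unadjusted intervals raise the chance of a false pain signal, which is acceptable for a harm outcome. The within-training change has no untreated control, so it describes worsening and does not show that training caused it. Precision also stays modest: with 18 completers the interval reaches about 0.50 SD either side of the mean.

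### The power of more than 80% is computed at alpha 0.05 for MEP amplitude alone, but the plan's Bonferroni rule means that no primary outcome is tested at 0.05

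*Protocol*

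**What the plan says.** All the relevant text is in the protocol, section 3.

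- **Power Calculation.** The effect assumption concerns MEP amplitude: "we project an improvement of 50% with MULTIMODAL training versus 25% with TREADMILL training". The spread is given as "We conservatively project an estimated variance of 25% for each group". Power is for a "difference between the two training groups on a two-tailed independent-sample *t*-test or Mann-Whitney test" and is stated to be "greater than 80% with 18 subjects" at alpha 0.05. Enrolment is set at 24 to allow for up to 25% dropout. The calculation does not mention multiplicity, and no power is given for the lower extremity motor score (LEMS).
- **Statistical Analysis.** There are two primary outcomes, change in MEP amplitude and change in LEMS. Of the rest it says "All other outcomes are secondary and exploratory". The same section closes its analysis rules with "Statistical significance for all outcomes will be corrected for multiple comparisons using Bonferroni's method".
- **Secondary outcomes.** The list has 14 numbered items, several of which hold more than one measure.

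**The concern.** The sample size and the decision rule use different significance levels for the same primary comparison. Any Bonferroni correction that includes both primaries tests MEP amplitude at 0.025 or less. Taken literally, the rule also makes the primaries share alpha with outcomes that the plan itself labels exploratory.

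Two things are at stake. First, a null result would be reported as coming from a trial with more than 80% power when the test applied had less. Second, because the number of comparisons is not fixed, the threshold for the primary outcomes could be settled after the data are seen.

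**Working it through.** **Inputs, all from the protocol**

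- Difference: 50 − 25 = 25 percentage points.
- SD: 25 points per modality. The protocol calls this a variance. Read as an SD it reproduces the stated power; an SD of 50 would give only about 31%.
- Observations: 18 per modality, since each completer contributes a percent change under both trainings. With 9 per group, power would be 51%, which does not match the claim.
- Test: two-sided, independent samples.
- Enrolment: 18 / (1 − 0.25) = 24, as stated.
- Number of outcomes: 2 primaries + 14 numbered secondary items = 16.

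**Formula**

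Noncentral t with df = 2n − 2 and noncentrality δ = difference / (SD × √(2/n)). Power = P(|T| > t at 1 − α/2).

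For n = 18: δ = 25 / (25 × √(2/18)) = 3.00, df = 34.
For n = 24: δ = 25 / (25 × √(2/24)) = 3.46, df = 46.

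**Step 1: reproduce the stated figure.** At α = 0.05 and n = 18 the critical value is 2.032 and power is 83.0%. A normal approximation gives 85.1%, and a Mann-Whitney test (n scaled by 0.955) gives 81.2%. The claim of more than 80% reproduces.

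**Step 2: apply the plan's own correction**

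| Family | α per test | Critical t (n = 18) | Power, 18 completers | Power, 24 completers |
|---|---|---|---|---|
| None (as in the power calculation) | 0.05 | 2.032 | 83.0% | 92.4% |
| Two primaries | 0.05/2 = 0.025 | 2.345 | 74.1% | 87.0% |
| Two primaries + 14 items | 0.05/16 = 0.003125 | 3.181 | 44.2% | 63.5% |

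At 18 completers the other two methods agree in direction. For two primaries, the normal approximation gives 77.6% and Mann-Whitney 71.8%. For 16 outcomes they give 51.8% and 41.3%.

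**Step 3: allow for within-person correlation.** The protocol states none, so this is an assumption. I simulated the planned independent-sample t-test on correlated pairs with 18 completers:

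| Assumed correlation | α = 0.025 | α = 0.05/16 |
|---|---|---|
| 0 | 74% | 44% |
| 0.3 | 78% | 43% |
| 0.5 | 81% | 43% |

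Correlation narrows the distribution of the test statistic around 3.00. That helps when the critical value lies below 3.00 (2.345) and does not help when it lies above (3.181).

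**Step 4: completers needed for 80% power** (t-test, zero correlation). At α = 0.025: 21 completers, or 21/0.75 = 28 enrolled. At α = 0.05/16: 32 completers, or 32/0.75 = 42.7, so 43 enrolled.

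**The case against.** The strongest reply has three parts.

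**The family may be narrower than 16.** The plan calls everything beyond the primaries exploratory, so the correction could be meant within tiers, and details of a family are often left to an SAP. This stands in part: the denominator is not stated, so 44% follows from the literal wording and is not a figure that the protocol fixes. It does not remove the conflict. The sentence covers all outcomes without exception, and even the narrowest family that includes both primaries gives 74% on the plan's inputs. A later SAP could define the family, but it would not make the protocol's power statement match it.

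**18 completers is the floor.** This stands. With no dropout the two-primary figure is 87%. But the protocol attaches its own claim to 18, and at 24 the 16-outcome figure is still only 63.5%.

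**The same people receive both trainings.** This also stands for the two-primary reading: at a correlation of 0.5 the shortfall at 18 completers disappears. It does nothing for the 16-outcome reading.

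A reader might infer that the trial simply has 44% power, or that a true effect of the planned size is more likely to be missed than found. The document does not support that as a general statement. It needs both the single 16-outcome family and attrition close to the full 25%.

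**Conclusion.** The protocol is wrong as written: the sample-size justification uses alpha 0.05 for one outcome, and the analysis rule excludes that alpha for either primary.

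The size depends on a family that the text leaves open. At the planned 18 completers, power for MEP amplitude falls from 83% to 74% under the narrowest family (about 9 points) and to about 44% under the literal one (about 39 points). These figures assume an SD of 25 points, a true difference of 25 points, the stated t-test and zero within-person correlation. Full completion or substantial correlation could bring the two-primary figure back above 80%. Neither brings the 16-outcome figure there: it is 63.5% with 24 completers and near 43% with correlation at 18. Nothing here speaks to power for LEMS, for which the protocol gives no inputs.

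**What to change.** **Statistical Analysis:** limit the multiplicity correction to the two primary outcomes, by Holm or by Bonferroni at 0.025 each. State that the secondary outcomes, already called exploratory, will be reported as unadjusted estimates with confidence intervals and without claims of significance.

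**Power Calculation:** restate power at the alpha used. Under the stated test and zero correlation this is about 74% with 18 completers and 87% with 24. If Holm is chosen, 74% is the lower bound for MEP amplitude, since it is tested at 0.05 whenever LEMS has already been declared significant. Call the 25% figure an SD. If a within-person correlation is relied on, state it as an assumption.

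**Cost:** the change is to wording only, with a less favourable stated power and no confirmatory claims on secondary outcomes. If the sponsor wants to keep 80% at 0.025 without relying on correlation or on lower dropout, the cost is enrolment of 28 instead of 24.
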